### Objectives

The trial is nearing completion. Its primary objective is to demonstrate the non-inferiority of the proportion of individuals abstinent from street opioids after one year of methadone in patients inducted in primary care with those inducted in CSAPA. Patients who initiated methadone in primary care are expected to have better outcomes compared with those in CSAPA in terms of retention, quality of life and satisfaction after 1 year of methadone treatment.

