### Outcomes and instruments

Multiple sources were used for data collection at screening (week preceding recruitment and first/seventh day after recruitment), at recruitment (day zero or month zero), induction (from the first to the second week of treatment) and maintenance (third, sixth and twelfth months). Data collection methods (ongoing) include face-to-face interviews, phone interviews using a Computer Assisted Telephone Interview
[18] and self-administered questionnaires, all adapted and validated for the type of information to be gathered.

The Opiate Treatment Index (OTI), a multi-dimensional questionnaire based on patients’ self-report
[19] is being used to measure Methaville’s primary outcome. This consists in measuring the proportion of all participants abstinent from street opioids after 1 year of treatment. Some secondary outcomes are also measured. First, retention in treatment and occurrence of overdoses are assessed. The prevalence of other HCV risk transmission practices is also documented using a series of questions extracted from a standardized questionnaire specifically adapted for this purpose - the Blood-Borne Virus Transmission Risk Assessment (BBV-TRAQ)
[20,21] - and also the questionnaire used by Lucidarme et al. in their longitudinal study
[22,23]. Other data about indicators relevant for the purpose of this study have been collected: depressive symptoms (using the CES-D questionnaire
[24]), suicidal risk (the Beck Hopelessness Scale
[25]), impulsivity (the Barratt Impulsiveness Scale), sensation seeking (the Brief Sensation Seeking Scale (BSSS)
[26]), tobacco dependence (the Fagerstrom test
[27]), alcohol consumption (the AUDIT questionnaire
[28]), pain assessment (the Brief Pain Inventory
[29]), adherence to methadone prescription, patient-health care provider relationship
[30], opioid withdrawal (the subjective opioid withdrawal symptoms scale (SOWS)
[31]), quality of life (the 12-item Short-Form Health Survey (SF-12)
[32]), Attention Deficit Hyperactivity Disorder (Adult ADHD Self-Report Scale 6 item version
[33]), urinary drug screening, and finally socio-demographic information on history of incarceration and contact with associations. Quality assurance and data security measures were established and approved for this protocol on the 21^st^ of May 2008.

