### Statistical methods

The trial was initially designed as a non-inferiority trial aimed to show the non-inferiority of the proportion of *non-injectors* who started methadone in primary care compared to those who started it in a CSAPA. However, as the number of patients injecting opioids at recruitment was low, the primary outcome was changed as ‘the proportion of *patients abstinent from* of street opioids after 1 year’, and the dimension of the study was re-computed. These changes were approved by the Scientific Committee of the trial, the Independent Committee and the Ethical Committee (CPP).

Secondary outcomes are the occurrence of fatal and non-fatal overdoses and the percentage of retention in both arms. We also investigated the prevalence of other HCV transmission practices and the effectiveness of treatment in terms of adherence, social insertion, addictive behaviours, quality of life, psychiatric comorbidities, social insertion, reduction in criminal acts and cost effectiveness.

When data analysis is completed later in 2012, the computation of the 95% confidence interval for the proportion of patients abstinent from street opioids at M12 in the two arms will be based on Intention To Treat (ITT), with lost to follow-up considered as a therapeutic failure (opioid users). Additional analyses will be performed without ITT, focusing on the most recent available information about opioid use during treatment. Mixed generalized linear models analyses will be used to identify predictors of the different outcomes. Non-inclusion or non-termination biases will be controlled for using selection models - including Heckman type models
[37] - and other approaches to take into account for the drop out process
[38].

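### The non-ITT analysis, if based on the last on-methadone report, does not estimate abstinence at month 12 and shrinks any arm difference that arises through stopping, so it cannot support non-inferiority

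*Protocol article*

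**What the plan says.** Under Outcomes and instruments, the Protocol article defines the primary outcome through the Opiate Treatment Index (OTI): "This consists in measuring the proportion of all participants abstinent from street opioids after 1 year of treatment". Maintenance-phase data are collected at months 3, 6 and 12.

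Statistical methods makes the primary analysis ITT: "the computation of the 95% confidence interval for the proportion of patients abstinent from street opioids at M12 in the two arms". A patient lost to follow-up is scored as using opioids. The same paragraph then adds: "Additional analyses will be performed without ITT, focusing on the most recent available information about opioid use during treatment".

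Two other provisions in that section bear on the point:
- **Drop-out models.** "Non-inclusion or non-termination biases will be controlled for using selection models - including Heckman type models", "and other approaches to take into account for the drop out process". Mixed generalized linear models are also named, for predictors of the outcomes.
- **Retention by arm.** "Secondary outcomes are the occurrence of fatal and non-fatal overdoses and the percentage of retention in both arms".

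Objectives gives the expected direction of retention: "Patients who initiated methadone in primary care are expected to have better outcomes compared with those in CSAPA in terms of retention".

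**The concern.** The primary outcome is status at one year in everyone randomized. The non-ITT analysis, on its natural reading, uses status at the last report made on methadone. For a patient who stopped at month 4, that is the M3 report. An M6 or M12 interview held after stopping would not enter.

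The two quantities differ most in the patients for whom treatment did not last. If patients tend to do better on methadone than after leaving it, the last on-treatment report credits early stoppers with an abstinence that they may not have at M12. The credit is larger in the arm with more stopping, so the arms move together.

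In a superiority trial that would usually be conservative. In a non-inferiority trial, bias towards no difference favours the claim when the experimental arm is the one losing patients. A second analysis is useful here only if it could contradict the first, and this one is least able to do so when the deficit comes through stopping. The article's Discussion says that the result may change the legal framework for methadone induction, so a reassuring but uninformative second result could carry weight.

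**Working it through.** The article gives no figure for this analysis that could be reproduced, and no stopping rates. The check is therefore an illustration.

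**From the article:** margin 15 points (Sample size); arms of 48 (CSAPA) and 147 (primary care) (Abstract); reports at months 3, 6 and 12.

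**Assumed, the same in both arms:**
- p = 0.80, abstinent at M12 among those still on methadone
- t = 0.20, abstinent at M12 among those who stopped
- q = 0.60, abstinent at the last on-treatment report among those who stopped

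The proportion stopping is s, assumed 0.20 in CSAPA and 0.45 in primary care.

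**Formulas**
- True M12 abstinence = (1 − s)p + s·t
- Last on-treatment report = (1 − s)p + s·q

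**True M12 status**
- CSAPA: 0.80×0.80 + 0.20×0.20 = 0.68
- Primary care: 0.55×0.80 + 0.45×0.20 = 0.53
- Difference: −15 points

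**Last on-treatment report**
- CSAPA: 0.80×0.80 + 0.20×0.60 = 0.76
- Primary care: 0.55×0.80 + 0.45×0.60 = 0.71
- Difference: −5 points

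With stopping at 20% v 40%, the true figures are 0.68 v 0.56 (−12) and the last-report figures 0.76 v 0.72 (−4).

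**Why the share is constant.** With p, q and t equal across arms, the true difference is −(difference in s)×(p − t), and the last-report difference is −(difference in s)×(p − q). The share that survives is (p − q)/(p − t) = 0.20/0.60 = one third, whatever the stopping rates.

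**Range for q, with stopping at 20% v 45% (true difference −15)**

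| q | CSAPA | Primary care | Difference |
|---|---|---|---|
| 0.40 | 0.72 | 0.62 | −10 |
| 0.60 | 0.76 | 0.71 | −5 |
| 0.80 | 0.80 | 0.80 | 0 |

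**Direction.** Exchange the stopping rates, so that CSAPA loses 45% and primary care 20%. A true primary-care advantage of 15 points then becomes 5. With equal stopping the difference is 0 either way.

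**Against the margin, n = 48 and 147.** For 76% v 71%, the standard error is √(0.76×0.24/48 + 0.71×0.29/147) = 0.0721, so the Wald 95% lower limit is −0.05 − 1.96×0.0721 = −19.1 points, which misses −15. For 76% v 72% it is −18.1, also a miss.

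**Comparison with the ITT rule.** Here every stopper is assumed lost to follow-up, p = 0.80, and 10% of CSAPA and 30% of primary-care patients stop.

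| Analysis | CSAPA | Primary care | Difference | Lower limit |
|---|---|---|---|---|
| ITT, lost = failure | 72% | 56% | −16 | −31.0 |
| Last report, q = 0.40 | 76% | 68% | −8 | −22.2 |
| Last report, q = 0.60 | 78% | 74% | −4 | −17.7 |
| Last report, q = 0.80 | 80% | 80% | 0 | −13.0 |

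The ITT rule shows the whole gap. The last-report rule halves it or more, and meets the margin only at q = 0.80.

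**The case against.** Much can be said for the plan, and most of it stands.

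- **The primary analysis is not affected.** A reader might infer that a primary-care deficit would be hidden. The documents do not support that. ITT scores lost patients as failures, a patient who stopped but was interviewed at M12 would be classed by that interview, and retention is reported by arm. Any masking is confined to an analysis labelled additional, and the article does not say that it decides non-inferiority.
- **It is not the only companion to ITT.** Selection models and other drop-out approaches are planned in the same section. This stands. The article does not, however, tie them to the non-inferiority difference, and they do not alter what the last-report analysis measures.
- **The expected direction is the opposite.** A reader might take Objectives to predict the harmful case. It expects better retention in primary care, in which case the rule erodes an advantage of the experimental arm. This stands. The distortion runs either way, and the plan should also hold if that expectation is wrong.
- **The wording is open.** During treatment could mean the treatment year and not time on methadone. Off-treatment interviews would then count and that part of the objection falls. Nor does the article state outright that the last report is scored as the one-year result. The on-methadone reading is the natural one, but it is a reading.
- **The rates are assumed.** This stands. In the main example the lower limit still misses the margin, so no false conclusion of non-inferiority is shown there.
- **Detail left to other documents.** An article may leave out a per-protocol definition or a statement that interviews continue after stopping. Neither absence is counted here.

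**Conclusion.** The point holds for the supportive analysis only. Read as on-methadone status, the non-ITT analysis does not estimate M12 abstinence, and it pulls the arms together wherever they differ through stopping. On the assumed rates, a 15-point deficit becomes 5 and a 12-point deficit becomes 4. With q from 0.40 to 0.80, the 15 points become 10 to 0.

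This rests on three assumptions: that stoppers are abstinent more often at their last on-treatment report than at M12, that they do no better at that report than completers do at M12, and that these proportions are alike in the two arms. A difference between completers would not be removed.

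Agreement between this analysis and ITT should therefore not be read as confirming non-inferiority. The documents do not support the stronger inference that the trial's conclusion is biased towards non-inferiority.

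**What to change.** Change the wording of Statistical methods before the arms are compared:

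1. Make the supportive non-ITT comparison one that uses every M3, M6 and M12 OTI report whether or not the patient is still on methadone. Handle missing M12 status with the mixed or selection models already named, and apply them to the between-arm difference that is judged against the 15-point margin.
2. Add a per-protocol analysis on observed M12 status.
3. Keep the last on-treatment report as descriptive only, and say whether during treatment means on methadone or within the treatment year.

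The cost is a little more analysis work. The reports come from interviews already in the schedule, and the model classes are already in the plan.

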**Figure 1 F1:**
[figure not shown]
Flowchart for patient inclusion and study design.

## Discussion

To date, the ANRS-Methaville study is the first in France to be requested by a governmental agency with the objective of potentially changing the existing legal framework of an opioid maintenance treatment (OMT). We hope that methadone will be initiated by trained primary care physicians and in turn, that it will contribute to providing improved access to methadone in France.

However, the risk of overdose occurring during the induction phase of treatment
[39] highlights the requirement for closer follow-up early on, together with the systematic training of volunteer physicians. For many years now, in the United Kingdom, methadone has been mostly prescribed in primary care (as opposed to special centres)
[9]. This system of access to methadone has shown its effectiveness but also the risks associated with widespread access
[40,41]. In Scotland, methadone dose supervision in community pharmacies is currently in place
[10,42].

This is why the present trial is based not only on guidelines for methadone prescription and provision in primary care but also on a shared-care model.

Primary care physicians should work within a drug dependence care network and/or specialized centre, such as a CSAPA, and have documented experience of care for drug users. In addition, pharmacists must have direct contact with the methadone prescribing physician and must be involved from the beginning of the trial in order to guarantee effective supervision and follow-up of patients. This important responsibility may integrate pharmacists more into the health care system for drug users. Some previous studies have already shown that pharmacists appear to be in favour of providing OMT, supervising intake
[43] and playing an important role in treatment delivery, including referring difficult patients to other services
[44]. This potentially enhanced role for pharmacists is a unique opportunity to develop and improve the harm reduction network through the training of pharmacists.

This study may inform the development of any improved structuring of the existing framework for OMT induction in primary care through training and networking between physicians and pharmacists. The improved treatment efficacy of involving pharmacists as a key component of prevention for drug users has already been shown through the widespread provision of sterile injecting equipment
[45].

In this trial, because the recruitment of primary care physicians had to be carried out in close collaboration with a drug and alcohol centre, it was impossible to include primary care physicians in sites without any CSAPA (especially in rural settings where primary care physicians are mostly general practitioners). The representativeness of the study sample would certainly have been better if we had been able to include such rural-based physicians. However, we can hypothesize that whatever results we find will also be applicable to these latter as our intervention included pre-training for all the physicians who initiated methadone treatment.

This trial is a unique opportunity to encourage increased access to OMT, especially for opioid dependent individuals who do not have access to methadone for geographical reasons or for reasons of preference. In addition, it is an innovative experiment in France using preventive intervention research in opioid dependent individuals.

## Abbreviations

AFSSAPS: French Agency of Pharmaceutical Products; ANRS: Aids Agency; CEIP: Centre of evaluation and information on drug dependence; CMM: Centre of methodology and management; CPP: Committee and the Ethical Committee; CSAPA: Medical centre for drug and alcohol dependence; HCV: Hepatitis C virus; HIV: Human immunodeficiency virus; IDU: Injecting drug user; INSERM: National Institute of Health and Medical Research; ITT: Intention to treat; MINI: Mini-International Neuropsychiatric Interview; OMT: Opioid Maintenance Treatment; OTI: Opiate Treatment Index.
